### Aims and hypotheses

The aims of the PREPARE study are:
To test the hypothesis that risk stratification of women with suspected or confirmed pre-eclampsia based upon objective criteria reduces the proportion of medically-indicated preterm deliveries and improves neonatal outcomeTo evaluate whether use of and adherence to a Knowledge Transfer system will help to reduce preterm births in preeclampsiaCollect samples and individual patient data to establish a database and biological sample bank to search for unique risks and pathophysiological features. This will facilitate future studies and allow direct comparisons of demographic, metabolic and genetic factors in Brazil, other LMIC (Low and medium-income countries) and in HIC

## Methods/design

This is a stepped wedge cluster randomised trial for the implementation of an intervention at hospital level to evaluate whether a risk stratification model can reduce the incidence of preterm deliveries among women with suspected or confirmed preeclampsia. The trial will be conducted in seven tertiary centres, geographically dispersed throughout Brazil, and will run for 48 months; with data collection for 32 months. The participating tertiary centres and respective cities are: Fernandes Figueira Institute, Rio de Janeiro; Maternity Maria Amélia Buarque de Holanda, Rio de Janeiro (these two hospitals constitute one centre for the study); Maternity Leila Diniz, Rio de Janeiro; Botucatu Medical School, Botucatu-SP; Center for Women’s Health – CAISM, Campinas-SP; Hospital Guilherme Álvaro, Santos-SP; Maternity Leonor Mendes de Barros, São Paulo; Hospital of Clinics of Porto Alegre-RS.

### Inclusion criteria

Women presenting with suspected or confirmed pre-eclampsia between 20 + 0 and 36 + 6 weeks’ gestation at any of the seven tertiary centres will be eligible. Women with any co-morbidity (e.g. chronic hypertension, renal disease, diabetes) will also be included. Pre-eclampsia will be defined as blood pressure (BP) ≥ 140 mmHg systolic or 90 mmHg diastolic on or after 20 weeks of pregnancy, plus proteinuria: more than 1+ on a qualitative dipstick, or ≥ 0.3 g/24 h or urine protein/creatinine > 30 mg/mmol. In the absence of proteinuria pre-eclampsia will be diagnosed if BP ≥ 140/90 mmHg in the presence of any relevant maternal symptoms, signs (e.g., severe hypertension), abnormal maternal laboratory criteria (e.g., low platelets), or abnormal fetal wellbeing (e.g., fetal growth restriction) [29].

### Exclusion criteria

Women presenting with diagnosis of fetal demise at admission, non-reassuring fetal status necessitating urgent delivery at admission, eclampsia, HELLP syndrome, renal, cardiac or respiratory failure, coma, active labour, abruption or emergent delivery for other indications will not be included in the risk stratification component of the study. Although these women will not be managed according to risk assessments, their data will be collected to understand the magnitude of the problem of uncontrollable emergencies related to preterm PE. In view of the complexities of preterm delivery with multifetal gestations independent of PE and the lack of established cut off values for the intervention proposed, this group of women will not be included. We will however collect data from this group for sensitivity analysis with the potential for later analysis.

### Randomisation, recruitment and collection of baseline data

Randomisation will be undertaken by the trial statistician through a computer-generated blocking list at the start of the trial, but the timing of implementation of the intervention to each centre will be revealed only 30 days before the transition phase.

Recruitment will be performed by responsible doctors at each centre. At the start of the trial period, all women with suspected or diagnosed pre-eclampsia will be managed according to current local protocols. Subsequently, every four months, one centre will enter the transition phase to the implementation of the intervention (Fig. 1). All centres will continue the baseline data collection until randomised to implementation. Once each centre has crossed over to the intervention, it will continue to implement the intervention as part of routine care until the end of the study. After the last centre has crossed over, the trial continues a final four-month period during which all centres will be implementing the intervention. The effectiveness of the intervention will be measured by comparing the aggregated data of the centres in the pre-implementation phase of the trial with those in the post-implementation phase.

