**Methods:**

This is a stepped wedge cluster randomised trial that will include women with suspected or confirmed PE between 20 + 0 and 36 + 6 gestational weeks. All pregnant women presenting with these findings at seven tertiary centres in geographically dispersed sites, throughout Brazil, will be considered eligible and evaluated in terms of risk stratification at admission. At randomly allocated time points, sites will transition to risk stratification performed according to sFlt-1/PlGF (Roche Diagnostics) measurement and fullPIERS score with both results will be revealed to care providers. The healthcare providers of women stratified as low risk for adverse outcomes (sFlt-1/PlGF ≤38 AND fullPIERS< 10% risk) will receive the recommendation to defer delivery. sFlt-1/PlGF will be repeated once and fullPIERS score twice a week. Rates of prematurity due to preeclampsia before and after the intervention will be compared. Additionally, providers will receive an active program of knowledge transfer about WHO recommendations for preeclampsia, including recommendations regarding antenatal corticosteroids for foetal benefits, antihypertensive therapy and magnesium sulphate for seizure prophylaxis. This study will have 90% power to detect a reduction in PTB associated with PE from a population estimate of 1.5 to 1.0%, representing a 33% risk reduction, and 80% power to detect a reduction from 2.0 to 1.5% (25% risk reduction). The necessary number of patients recruited to achieve these results is 750. Adverse events, serious adverse events, both anticipated and unanticipated will be recorded.

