**Fig. 1 Fig1:**
[figure not shown]
Description of randomisation and implementation of the intervention for the Stepped Wedge design. There will be an initial four-month period of baseline data collection at hospitals, during which none of the centres will be exposed to the intervention. Subsequently, every four months, one centre will be randomised to the intervention. Four months prior to implementation, the centre will be engaged in a programme of intensive knowledge transfer, followed by one month of transition

Routine clinical data will be collected for the trial on all pregnant women with suspected or diagnosed pre-eclampsia that present to the participating centres between 20 + 0 and 36 + 6 weeks’ gestation.

In addition, they will be invited to sign the informed consent form, and provide additional samples for research purposes.

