### Statistical issues

#### Sample size

The primary aim is to test whether care targeted at preventing unnecessary delivery of women with pre-eclampsia will reduce the proportion of women delivered in the centres with preterm pre-eclampsia (deliveries with preterm pre-eclampsia/total deliveries). The power calculation depends on estimates of the total number of births, current pre-eclampsia prevalence and proportion with preterm deliveries from the seven centres (which have already agreed to participate). We estimate the mean number of infants born in each month per centre to be 330, and that of these ~ 5% will be born to women with pre-eclampsia. The preterm rate among those women with pre-eclampsia is approximately 36%. Therefore each month, there will be the potential to enter 17 women with pre-eclampsia, of whom approximately 6 would deliver prematurely, and outcome data will be available for approximately 700 deliveries of women with preterm pre-eclampsia. There is limited information on likely intracluster correlation (ICC) for this outcome in this setting and so we have explored sensitivity to a range of values.

Power calculations for stepped wedge cluster trials were as described in Hussy and Hughs [18]. Assuming that seven centres take part and allowing for a one month transition phase, and that in each centre there are approximately 17 cases of pre-eclampsia and 330 deliveries per month (with outcome data available for all deliveries), this study will have 89.6% power to detect a reduction in preterm deliveries associated with pre-eclampsia in the study centres from a population estimate of 1.5 to 1.0%, representing a 33% risk reduction, and 79.6% power to detect a reduction from 2.0 to 1.5% (25% risk reduction). Although the ICC is included in the power calculation, the design was found to be insensitive to the ICC and sensitivity analyses showed that these calculations were robust to larger magnitudes of ICCs.

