### Data analysis

Hospital baseline characteristics of pregnancy outcomes to be collected throughout the data retrieval period will include numbers of women developing pre-eclampsia, women with preterm pre-eclampsia, gestational age at delivery of all hospital deliveries, and maternal and neonatal inpatient nights in women with pre-eclampsia. These baseline characteristics will be compared between exposure and non-exposure to the intervention and will be summarised by their means and standard deviations, medians and inter-quartile ranges, or numbers and percentages as appropriate. Centres will be classified as being exposed to the intervention one month after the centre was randomised to the intervention, and outcomes during the transition months will not be included.

The primary goal of the study is to test whether a care pathway targeted at preventing unnecessary delivery of women with pre-eclampsia will reduce the proportion of women delivered in the centres with preterm pre-eclampsia (deliveries with preterm pre-eclampsia/total deliveries). In statistical terms this null-hypothesis (no difference) can be tested using a mixed effects logistic regression model, with an indicator of whether the centre was exposed to the intervention as the dependent variable. Important independent variables to consider are the clustering effect (i.e. effect of centre), calendar time effect (since the intervention is sequentially rolled-out) and an indicator of intervention exposure for each centre at each time point; in additional to adjustment for other characteristics. Both individual and cluster level covariates to be included in the adjustment will be pre-specified and will include maternal age, parity, pre-existing chronic hypertension or other risk factors for prematurity. Null hypotheses and analyses for secondary outcomes take a similar form to that for the primary outcome, with appropriate link functions in the generalized linear mixed model. Summary treatment effect estimates will be reported (odds ratios or risk ratios) along with 95% CIs. These models will be fitted using population-averaged models using mixed effects methods in Stata version 14.2 or later (StataCorp, College Station, Texas).

The final trial dataset access will be limited to the authors of this study protocol.

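### Effectiveness is described twice as a pooled before/after comparison, which conflicts with the protocol's own centre- and time-adjusted model and would be confounded if it were used as the effect estimate

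*Protocol article*

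**What the plan says.** Three parts of the protocol article bear on how the effect is measured.

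- **Randomisation, recruitment and collection of baseline data.** Effectiveness will be "measured by comparing the aggregated data of the centres in the pre-implementation phase of the trial with those in the post-implementation phase". The abstract's Methods paragraph is similar: "Rates of prematurity due to preeclampsia before and after the intervention will be compared".
- **Data analysis.** The primary null hypothesis is tested with a mixed effects logistic regression. "Important independent variables to consider are the clustering effect (i.e. effect of centre), calendar time effect (since the intervention is sequentially rolled-out"), followed by an indicator of exposure for each centre at each time point and adjustment for other characteristics. Secondary outcomes follow a similar form.
- **Sample size.** Power comes from the standard stepped wedge method, "Assuming that seven centres take part and allowing for a one month transition phase". It is given as 89.6% for a fall from 1.5% to 1.0% and 79.6% for a fall from 2.0% to 1.5%.

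No section says that the aggregated comparison is only descriptive, or which of the two gives the primary effect estimate.

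**The concern.** In a stepped wedge design, control data come mainly from early months and late-crossing centres, and intervention data from late months and early-crossing centres. A comparison of all pre-implementation data with all post-implementation data therefore contains the intervention effect, any background change in the rate of preterm pre-eclampsia deliveries, and any difference between centres. It also makes no use of the randomised crossing order. The adjusted model separates these components.

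A published protocol is what the final report is judged against. As the text stands, an unadjusted before/after result could be presented as following the protocol, and so could the model-based result, although the two can differ materially.

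**Working it through.** **1. Which analysis the stated power belongs to.** Inputs from the article: 7 centres, 32 months, one centre crossing every 4 months, 330 deliveries per centre-month, one transition month per centre dropped. Assumed, because the article gives neither: two-sided alpha 0.05 and an intracluster correlation (ICC) from 0.001 to 0.05. The variance of the exposure coefficient is the generalised least squares variance with a random centre effect and, where stated, fixed monthly period effects.

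| Analysis | 1.5% → 1.0% | 2.0% → 1.5% |
|---|---|---|
| Stated in the article | 89.6% | 79.6% |
| Period effects, binomial variance at the control rate | 85.9–88.1% | 75.1–77.9% |
| Period effects, binomial variance at the mean rate | 91.3–93.0% | 80.4–83.0% |
| No period effects, variance at the control rate | 99.7–99.8% | 98.3–98.6% |
| Pooled two-proportion test | 99.998% | 99.9% |

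The stated figures lie between the two time-adjusted rows. Without time in the model, power was at least 98.3% in every variant tried (ICC 0 included). The planned power is therefore that of a time-adjusted analysis.

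**2. Calendar gap in the pooled comparison.** The schedule is "There will be an initial four-month period of baseline data collection at hospitals, during which none of the centres will be exposed to the intervention", then "Subsequently, every four months, one centre will enter the transition phase to the implementation of the intervention", "with data collection for 32 months". This fits 4 + 7 × 4 = 32 months.

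- Control centre-months: 4 + 8 + 12 + 16 + 20 + 24 + 28 = 112, mean calendar month 10.0 (month mid-points).
- Intervention centre-months, transition month dropped: 27 + 23 + 19 + 15 + 11 + 7 + 3 = 105, mean month 22.4.
- Gap: 22.4 − 10.0 = 12.4 months (12.0 if transition months are kept).

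**3. Centre mix.** The first centre to cross contributes 4 control and 27 intervention months; the last contributes 28 and 3. If centre rates were spread evenly from 1.0% to 2.0% (an assumption), with no trend and no effect, the pooled risk ratio would range from 0.79 (lowest-rate centres crossing first) to 1.26 (highest-rate centres crossing first).

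**4. Illustration of a background trend, true effect nil.** The monthly rate is p0 × (1 − annual fall)^(month/12). Deliveries: 112 × 330 = 36,960 control and 105 × 330 = 34,650 intervention.

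Example with p0 = 1.5% and a 10% annual fall:
- mean control rate 1.376%, mean intervention rate 1.235%, risk ratio 1.235/1.376 = 0.90;
- pooled rate 1.308%, standard error √[0.01308 × 0.98692 × (1/36,960 + 1/34,650)] = 0.00085;
- expected z = 0.00141/0.00085 ≈ 1.66, so a test at ±1.96 rejects in about 38% of trials.

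Ranges over base rates of 1.5–2.0%, from this formula and from simulated null trials:

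| Assumed setting | False rejection, pooled test |
|---|---|
| 10% yearly fall, with or without centre variation | about 38–53% |
| 5% yearly fall, no centre variation | about 13–17% |
| 2% yearly fall, no centre variation | about 6–7% |
| No trend, between-centre coefficient of variation 10–23% | about 10–32% |

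In simulated null trials with yearly falls of 0–10% and a centre coefficient of variation up to 23%, a model with centre and period effects rejected in about 4–7%.

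**The case against.** The strongest reply is that the protocol already plans the right analysis. The aggregated-data sentence closes a section on randomisation and recruitment and names no statistic or test; the abstract sentence is a summary. The Data analysis section restates the primary goal, gives a model, lists calendar time and explains why it is needed. The power calculation agrees. On that view the two sentences are loose summaries of an exposed-versus-unexposed contrast.

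Most of this stands, and it rules out three stronger readings that a reader might infer:

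- **That the primary analysis is an unadjusted two-proportion test.** No section says so, and the model and the power basis point the other way.
- **That calendar time is optional because it is only listed for consideration.** The exposure indicator stands in the same list under the same verb and cannot be optional. The later reference to adjustment for other characteristics implies that the listed terms are themselves adjusted for.
- **That any national trend will be reported as an intervention effect.** This would happen only if the pooled comparison were used as the estimate.

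What the reply does not remove is the contradiction. The sentence is worded as the rule by which effectiveness is measured, the abstract has a similar one, and nothing subordinates either to the model. The Data analysis section also calls exposure the dependent variable. That is a separate slip, but it makes the section a less clear authority than it should be.

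**Conclusion.** The point holds as an internal contradiction. The before/after wording in the recruitment section and the abstract conflicts with the adjusted model in Data analysis and with the power basis in Sample size. The 12-month calendar gap and the centre imbalance follow from the article's own schedule and need no outside assumption.

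The harm is conditional: it arises only if the pooled comparison is reported as the effect estimate. Its size depends on trends, centre variation and base rates that the article does not give, so the error rates above are illustrations. Under a 10% yearly fall the spurious reduction of about 10% is roughly a third of the 33% target. Under a 2% yearly fall with no centre variation, false rejection is barely above the nominal 5%.

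**What to change.** 1. In the abstract and in the section on randomisation and recruitment, replace the before/after sentences with: 'Effectiveness is the exposure coefficient from the mixed model with centre and calendar-period effects described under Data analysis; pooled before/after rates are descriptive only.'
2. In Data analysis, state that centre, calendar period and exposure will be included in the primary model, in place of the wording that lists them for consideration.
3. Adjust secondary outcomes for time in the same way where event counts allow, with a simpler time term for rare outcomes such as maternal death, stroke or coma. A full set of period effects in every secondary model would ask too much of sparse data.

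The cost is wording only. Design, data collection and stated power are unchanged by this fix.

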**Fig. 1 Fig1:**
[figure not shown]
Description of randomisation and implementation of the intervention for the Stepped Wedge design. There will be an initial four-month period of baseline data collection at hospitals, during which none of the centres will be exposed to the intervention. Subsequently, every four months, one centre will be randomised to the intervention. Four months prior to implementation, the centre will be engaged in a programme of intensive knowledge transfer, followed by one month of transition

Routine clinical data will be collected for the trial on all pregnant women with suspected or diagnosed pre-eclampsia that present to the participating centres between 20 + 0 and 36 + 6 weeks’ gestation.

In addition, they will be invited to sign the informed consent form, and provide additional samples for research purposes.

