Changing the behaviour of care providers presents substantial challenges [16–22]. This is especially difficult in a setting in which we are changing what is likely perceived as a “less risky” to “more risky” approach with respect to maternal health. To address this challenge, a program of Knowledge Transfer (KT) will be introduced to all healthcare professionals involved with the management of pre-eclamptic patients in the participating centres [23, 24]. This program has been developed and tested by the Canadian Institutes of Health Research [25]. This KT will include information specifically relevant to the intervention. Thus it will include information about the excess of preterm births for precclampsia in Brazil, the hazards of preterm birth, the data upon which the intervention is based and the safety meausure instituted to assure the safety of the intervention.

In addtion, the PREPARE KT model will be based on the World Health Organization (WHO) recommendations for pre-eclampsia/eclampsia management, including the use of low-dose aspirin and calcium supplementation for prevention of pre-eclampsia. Evidence from meta-analyses indicates that calcium supplementation reduces the risk of pre-eclampsia by half (and even more in high-risk women). The benefit of aspirin is more modest with a 17% reduction in the risk of pre-eclampsia (25% in high-risk women) [3]. In Brazil calcium supplementation is given to less than 10% of women in whom it is indicated [26]. A recent work demonstrated high prevalence of inadequate calcium in two cohorts of pregnant women evaluated in Brazil [27].

Educational modules specific to the application and use of fullPIERS and sFlt/PlGF in the context of the trial will also be provided prior to implementation of the risk assessment strategy at each participating centre.

The PREPARE study will be implemented following a stepped wedge design. Clusters (in this case tertiary hospitals with maternity units) are identified to take part in a one-way cross-over cluster RCT and, before the trial begins, randomly allocated a start date from when they are given the intervention. The time they receive the intervention is randomly ordered [28]. The clusters crossover at regular intervals (in this case, every four months), from their current standard of care to the intervention program. The randomisation sequence is decided before the start of the trial, and is made known to each centre shortly before implementation.

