### Knowledge transfer program

The activities for the Knowledge transfer (KT) program will be established in phases and constitute a strategy to improve commitment with recruitment and adherence to the study protocol.

Phase 1: the KT will address the problem of unnecessary delivery of women with preterm PE, its impact on fetal outcome and its magnitude in Brazil. The scale of and evidence for the problem will be presented to healthcare providers together with the proposed solution and its supporting information.

Phase 2: several strategies will be used of which the key component is the e-learning module [25]. One module will present the problem and supporting data and a second will outline the solution through the use of sFlt-1/PlGF and full-PIERS to grade the risks of delayed delivery. In both modules relevant data (including downloadable PDFs of an overview and/or the original manuscripts) will be available. All care providers in the participating centres will be expected to utilize this resource. Staffs who have omitted to use them will be prompted to do so. The final module will ‘test’ what has been learned and those who pass will be awarded a formal signed certificate of proficiency. The e-learning will be available to the providers at the time of the transition phase of the intervention. Seminars and meetings will complement these strategies.

Phase 3: the KT strategy for the study will be outlined and discussed. Participants will be asked to assess potential barriers, which can be minimised in future training interactions for Phase 4.

Phase 5: the use of the knowledge will be monitored and graded as monthly assessment during the intervention. Aspects regarding number of preterm births, whether all women for whom the intervention was indicated were treated and whether the information was used appropriately will be important points. If there is a suggestion that the intervention is not being performed when indicated or not used appropriately we will institute face-to-face seminars to identify and modify obstacles. The identification of specific practitioners who are accounting for the deficiencies we will meet with them for focussed determination of specific obstacles.

Phase 6: this phase will focus on clinical outcomes monitoring.

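### Knowledge-transfer timings conflict, and as written the months of intensive knowledge transfer before each switch are analysed as unexposed control

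*Protocol article*

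**What the plan says.** Four parts of the protocol article bear on when KT starts and how those months are analysed.

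- **Fig. 1 legend:** "Four months prior to implementation, the centre will be engaged in a programme of intensive knowledge transfer, followed by one month of transition". The same legend describes an initial four-month baseline with no centre exposed, after which one centre crosses every four months.
- **Randomisation, recruitment and collection of baseline data:** "the timing of implementation of the intervention to each centre will be revealed only 30 days before the transition phase". Also "All centres will continue the baseline data collection until randomised to implementation", with effectiveness judged by "comparing the aggregated data of the centres in the pre-implementation phase of the trial with those in the post-implementation phase".
- **Knowledge transfer program:** "The e-learning will be available to the providers at the time of the transition phase of the intervention". That section treats e-learning as the main element of its second phase.
- **Data analysis:** on exclusions, "outcomes during the transition months will not be included"; no other months are excluded. On the start of exposed status, the section has this rule: "Centres will be classified as being exposed to the intervention one month after the centre was randomised to the intervention".

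On what KT contains, the Background says: "Thus it will include information about the excess of preterm births for precclampsia in Brazil, the hazards of preterm birth". Aims and hypotheses makes the effect of KT on preterm births a trial aim, and the Intervention section describes KT as crucial to the study.

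**The concern.** Two things do not fit.

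First, the timings. A centre that enters its own intensive KT programme four months ahead can work out its switch date about three months before the 30-day disclosure. A main KT element released only at transition also sits badly with a four-month lead.

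Second, the exposure coding. KT teaches providers that too many women with pre-eclampsia are delivered early, which bears directly on the decision behind the primary outcome. Providers could act on it before any test result is revealed. Yet the only excluded window is the transition month, so by default the KT months count as usual care. In a stepped-wedge model with calendar-time effects, the periods on either side of each switch carry much of the information. A partly treated last control period would therefore pull the estimate towards zero and lower power, by an amount that depends on how much KT achieves alone.

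**Working it through.** **Inputs from the protocol.** 7 centres, 32 months of data, one centre crossing every 4 months after a 4-month baseline, a 1-month transition removed, and 330 deliveries per centre-month. Target effects are 1.5% to 1.0% (stated power 89.6%) and 2.0% to 1.5% (stated power 79.6%).

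**Assumptions, not in the protocol.** Two-sided alpha 0.05; ICC from 0 to 0.1; binomial variance at the mean of the two rates; f, the share of the full effect already present during KT.

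**Layout.** Centre k crosses after month 4k.
- Control centre-months: 4 × (1 + 2 + … + 7) = 112.
- Transition: 7. Exposed: 7 × 32 − 112 − 7 = 105.
- KT months in control: 7 × 4 = 28, or 28/112 = 25%. If the four months include the transition month: 7 × 3 = 21, or 21/112 = 19%.

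**Reproducing the stated power.** Hussey–Hughes weighted least squares (random centre effect, fixed time effects, one treatment term), power = Φ(δ/SE − 1.96). With monthly time effects and ICC 0.05 to 0.1 this gives 91.3% and 80.3–80.4%, within 2 points of the stated 89.6% and 79.6%. The stated power is therefore not in dispute, but it presumes uncontaminated control months.

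**Base case used below** (four-month period effects, ICC 0.01):
- 1.5% to 1.0%: SE = 0.001493, so Φ(0.005/0.001493 − 1.96) = Φ(1.39) = 91.8%.
- 2.0% to 1.5%: SE = 0.001762, so Φ(0.005/0.001762 − 1.96) = Φ(0.88) = 81.0%.

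**Attenuation.** If the KT months carry f times the full effect but are coded as control, the expected coefficient is linear in f. At ICC 0.01, estimate/truth = 1 − 0.692 f with four KT months in control, and 1 − 0.519 f with three. Power becomes Φ(ratio × δ/SE − 1.96). Worked case, f = 0.25 with four months: ratio = 1 − 0.692 × 0.25 = 0.827, and power = Φ(0.827 × 3.35 − 1.96) = Φ(0.81) = 79%.

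| f | Estimate/truth, 4 KT months | Power 1.5→1.0% | Power 2.0→1.5% | Estimate/truth, 3 KT months | Power 1.5→1.0% | Power 2.0→1.5% |
|---|---|---|---|---|---|---|
| 0 | 1.00 | 92% | 81% | 1.00 | 92% | 81% |
| 0.1 | 0.93 | 88% | 75% | 0.95 | 89% | 77% |
| 0.25 | 0.83 | 79% | 65% | 0.87 | 83% | 70% |
| 0.5 | 0.65 | 59% | 46% | 0.74 | 70% | 56% |

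**Sensitivity to ICC** (four KT months, f = 0.5): ratio 0.81 at ICC 0, 0.75 at 0.0001, 0.68 at 0.001 and 0.65 at 0.05 to 0.1.

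**Crude pooling.** A plain before-and-after comparison would shrink only by 0.25 × f, to 1 − 0.25 × 0.5 = 0.875 at f = 0.5. The time-adjusted model named in Data analysis is hit harder.

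**Cost of remedies** (ICC 0.01, unbiased for the full package against usual care):
- Exclude one KT month plus the transition month: 89.6% and 77.9%, against 91.8% and 81.0%. The match with the protocol's 89.6% is a coincidence; compare with the base case here.
- Exclude all four KT months plus transition: 77.7% and 63.6%.
- Give the KT months their own exposure term: 77.9% and 63.8%.

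**The case against.** The strongest reply is that no bias has been shown. Nothing in the protocol gives f, and at f = 0 the estimate is untouched. The text also offers reasons to expect a small f: e-learning arrives only in the excluded transition month, the Background admits that provider behaviour is hard to change, and it blames early delivery on poor diagnostic and risk-stratification tools, which KT alone does not supply. If all KT really began at transition, both problems would largely disappear. This stands. It makes the size conditional, but it does not reconcile the timings or say how the KT months are handled.

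A reader might infer more than the document supports:

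- **That the first centre has no clean control data.** This follows only if the four months precede transition. The legend can also be read as including it, which leaves that centre one clean month, and the figure itself is not shown.
- **That exposure is wrongly dated from randomisation at trial start.** The article repeatedly uses the word for reaching the allocated step. Read so, exposure begins after the transition month. This is a minor clarification.
- **That early knowledge of the date lets centres select patients.** The primary outcome uses all deliveries, and consent covers only ancillary samples, so there is little scope for selection. What remains is a conflict of wording.
- **That the timetable blurs the stratification aim with the KT aim.** The two are delivered as a package, so a two-state model cannot separate them whenever KT starts.

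Finally, the three-state remedy has a real price. At f = 0.25 with three KT months, leaving the months in control keeps 83% and 70% power with a conservative bias, more than the 78% and 64% from separate coding. This argues against making that coding the obligatory primary analysis.

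**Conclusion.** The concern holds in a limited form. The stated timings for KT, disclosure and e-learning are incompatible, and the exclusion rule is shorter than the KT period in Fig. 1. No sentence names the KT months as control; it follows because only transition months are removed and all earlier data are baseline.

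The bias is conditional. At ICC 0.01 the estimate would be between 100% of the truth (f = 0) and 65% (f = 0.5, four KT months), or 74% at f = 0.5 with three. The range assumes that the target is the full package against usual care, that the KT effect is constant over those months, and that the linear approximation used for power is adequate. It is milder at very low ICC. It would be wrong to say that the trial is biased by a third or that its power is 59%; those are the f = 0.5 case, which the documents do not support over smaller values. This is a should-fix.

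**What to change.** 1. Reconcile the Fig. 1 legend, the randomisation section, the Knowledge transfer program section and Data analysis into one timetable. State whether the four months include transition.
2. Define exposure from each centre's scheduled implementation date, which also settles the wording about randomisation.
3. Preferred: confine intervention-specific KT to the window after the 30-day disclosure, and exclude that month and the transition month from the primary analysis. At ICC 0.01 this costs 91.8 − 89.6 = 2.2 points and 81.0 − 77.9 = 3.1 points of power. A shorter KT programme might prepare centres less well; the documents do not allow that to be costed.
4. If four-month KT is kept, prespecify an analysis that excludes those months or gives them their own exposure term, at least as a sensitivity analysis, and report it beside the primary result. Its power is about 78% and 64% at ICC 0.01, below the stated 89.6% and 79.6%, so the power statement would need revising if it became primary.

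The changes are to wording, the analysis specification and KT scheduling. They should be settled before further centres begin KT, because usual-care control months cannot be recovered afterwards.
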